#### Analysis study 1A: effectiveness

To determine the effectiveness of RC attendance we will conduct multi-level regression analyses with three levels: (1) repeated observations (2) within participants and (3) participants in pairs of intervention and propensity score matched controls. While participants in the experimental group can be considered to occupy multiple sites (i.e. a multisite study), participants from the control group strictly seen cannot. Hence, through likelihood ratio testing it will be determined whether including an additional fourth level (random intercept) for site leads to a significant better model fit, in which all participants in the control group will be considered to reside at a single unique site. As no true pre-intervention randomization is possible, the effect analyses will be performed slightly modified to as what is recommended by Twisk, Bosman [66] in that the fixed effect for group will be included in the repeated measures models, alongside the fixed effect for time and the interaction between those. In addition, the models will be fitted without intercept, aiding in interpretation of potential (not intervention related) differences between the control and experimental group. All multi-level analyses will be performed using the R packages lme4 [67] and lmerTest [68].

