#### Research questions

To evaluate the (cost-)effectiveness of RCs, we pose the following research questions (RQs):

RQ 1: Does attending an RC impact empowerment on the long term, and if so, to what extent?

RQ 2: Does attending an RC impact other recovery related outcomes, such as quality of life, (mental) health, loneliness, satisfaction with treatment and support, and self-stigma on the long term, and if so, to what extent?

RQ 3: What is the cost-effectiveness of RCs?

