#### Population

All study participants (both experimental and control group) are people with mental vulnerabilities. RC students will be matched with panel members based on relevant key characteristics through propensity score matching [48].

**Inclusion Criteria.** To be included in the experimental group, people need to be current RC students at the moment of recruitment (in any role, so including volunteers and employees). Moreover, participants need to experience SMI or mental vulnerabilities (both self-reported or diagnosed).

**Exclusion Criteria.** Participants are not eligible if they do not sufficiently master the Dutch language to properly understand and fill out the surveys (even with assistance from the POP group experiential researchers). Specifically for the control group, participants will be excluded from the matching procedure if they are involved in an RC or similar initiatives (i.e., recovery-oriented consumer run organisations) at time of the baseline measurement. If panel members visit one of the included RCs at the time of recruitment, they will be allocated to the experimental group.

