Variables that will be used for the matching are gender, age, nationality, level of education and diagnoses (psychotic disorders, mood disorders, anxiety disorders, personality disorders, substance use disorders, neurodevelopmental disorders, eating disorders). If someone does not have an official diagnosis, we will use self-reported diagnosis as a proxy. Although potentially relevant, duration of service use will not be used as matching variable since true baseline data are unavailable; the experimental group may be already active at the RC for a significant amount of time at t_0,_ which may have impacted service use. Each participant from the experimental group will be matched to one or more participants from the control group. Given the large sample size of the control group and the limited number of matching variables, we will likely retrieve multiple good matches per RC partaker, reducing uncertainties and increasing reliability.

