#### Variables of interest study 1A and 1B

For clarity, the variables of interest are reported here for the effectiveness study (1A) and the economic evaluation (1B) separately. Demographic and descriptive variables are relevant for both studies 1A and 1B.

**Demographic and Descriptive Variables.** Basic demographics (gender, age, nationality, level of education, employment status, housing), and SMI-specific variables (mental health problems; self-reported and officially diagnosed, duration of mental health problems, health care use) will be used to describe the sample. As noted, many of these variables will be used to match participants from the control group (panel members) with participants from the experimental group (RC students). Furthermore, participants in the experimental group will indicate in what way and how frequently they are active at the RC.

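### Recovery College (RC) participants may already have benefited at t0, so the planned group-by-time contrast measures further change among current attenders, and the t0 gap cannot be labelled unrelated to the intervention

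*Protocol article*

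**What the plan says.** All references are to Study 1 of the protocol article.

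- **Research questions.** RQ 1 asks: "Does attending an RC impact empowerment on the long term".
- **Population.** For the experimental group, "people need to be current RC students at the moment of recruitment", in any role, volunteers and employees included. No limit is set on earlier attendance. For controls, "participants will be excluded from the matching procedure if they are involved in an RC or similar initiatives" at baseline.
- **Procedures, Matching.** Duration of service use is left out of the matching "since true baseline data are unavailable; the experimental group may be already active at the RC for a significant amount of time". The section adds that service use at t0 could thereby already have been affected.
- **Analysis study 1A.** The repeated-measures models contain fixed effects for group, time and group-by-time. They are fitted without an intercept, with the stated purpose of "aiding in interpretation of potential (not intervention related) differences between the control and experimental group".
- **Analyses.** Remaining baseline differences between the groups are to be checked and, where necessary, adjusted for.
- **Analysis study 1B.** A responder in the cost-effectiveness analysis is someone whose empowerment score shows reliable change between t0 and t4.

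**The concern.** The matching section accepts that the RC may have acted on participants before t0, and draws one consequence: it drops a matching variable. If service use at t0 can carry RC impact, so can empowerment at t0. The analysis section nevertheless attaches a label to group differences that leaves no room for this.

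What is at stake is the reading of the primary result. With a free group term, any gain made before t0 goes into the group difference at t0 and out of the group-by-time term. A participant who improved before t0 and kept the gain contributes no effect to the model and counts as a non-responder in the cost-effectiveness analysis. A null interaction could then be taken as an answer to RQ 1 when it concerns only what happened after t0. Adjusting for a baseline difference in the outcome would remove the same earlier gain.

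**Working it through.** **1. What the contrast estimates.** Let D be the total RC effect and f the share of it already present at t0. Ignoring selection, and with a constant group difference after t0:

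- expected group difference at t0 = f × D
- expected post-t0 group-by-time contrast = D − f × D = (1 − f) × D

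With selection, a further amount s is added to the t0 gap, which becomes s + f × D. The model returns only this sum. Nothing in the stated data or model separates s from f × D.

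**2. Inputs for size.** From the Sample size section: D = 0.3, correlation 0.6 between subsequent measurements, 30% dropout at t4, 125 per group, power 82.8%. From the Design section: empowerment is measured at t0, t2 and t4. Assumed, because not stated: first-order autoregressive (AR(1)) correlation, retention of 100%, 85% and 70% (linear dropout), two-sided alpha of 0.05, and one common group difference at t2 and t4. The share f is not in the documents.

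**3. Reproducing the plan's power.** Power = Φ(effect / SE − 1.96), with SE from the generalised least squares information matrix. With the group means constrained equal at t0 and the whole 0.3 appearing afterwards, SE = 0.1032, and Φ(0.3/0.1032 − 1.96) = 82.8%. This matches the stated figure, although the protocol does not say which contrast was simulated.

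**4. The stated model.** Adding the free group effect raises SE to 0.1183. The power is then:

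| Share f before t0 | t0 gap from prior benefit | Remaining contrast | Power, free group effect | Power, equal t0 means |
|---|---|---|---|---|
| 0 | 0 | 0.300 | 71.8% | 82.8% |
| 0.25 | 0.075 | 0.225 | 47.7% | 58.7% |
| 0.50 | 0.150 | 0.150 | 24.5% | 30.6% |
| 0.75 | 0.225 | 0.075 | 9.2% | 10.9% |

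The fourth column belongs to the model in the analysis section. The last is shown because it is the setting that reproduces 82.8%. The drop from 82.8% to 71.8% at f = 0 comes from the free group term alone, not from prior attendance.

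**5. Sensitivity to the dropout pattern.** With all dropout after t2, the free-group-effect figures are 76.8%, 52.4%, 27.0% and 9.9%. With all of it before t2, they are 65.6%, 42.5%, 21.8% and 8.5%. The pattern is the same.

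**The case against.** **Keeping a group term is defensible.** In a non-randomised comparison, crediting the t0 gap to the RC would count selection as benefit. Estimating change after t0 avoids that. This stands: the model need not be replaced, but its estimate must be described for what it is.

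**The label can be read narrowly.** The parenthesis does not mention t0, and may only specify which differences are meant. No passage calls t0 a pre-RC measurement; the matching section says the opposite. Nor does the analysis section name the group-by-time term as the effect; that is an inference from the model and from the t0-to-t4 responder rule. Even on the narrow reading, the model cannot isolate the part of the gap that is unrelated to the RC.

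**D = 0.3 may already be the post-t0 difference.** The Sample size section does not say. If so, prior attendance costs no further power, though the mismatch with RQ 1 remains.

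**Stronger readings that the documents do not support:**

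- *That the problem cannot be examined.* The article says "participants in the experimental group will indicate in what way and how frequently they are active at the RC" and names no start date. This is not a complete item list, and the questionnaire is not shown.
- *That people who left an RC before recruitment are wholly absent.* The Population section requires current students, but the paragraph on between-group differences also allows for recent involvement.
- *That new starters are counted in the wrong arm.* Someone starting around recruitment enters the RC arm. Only controls who start later remain controls. The Analyses section discloses this and foresees a possible sensitivity analysis, depending on numbers.

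**Conclusion.** The concern holds as a mismatch between the question and the contrast, and as a conflict between the matching section and the label in the analysis section. As planned, the group-by-time estimate and the responder outcome describe further change over 24 months among people already attending. They do not give the effect of attending an RC, and a null on either would not show that attendance is ineffective. Equally, the t0 gap cannot be credited to the RC, since part of it may be selection.

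The size is unknown. If 0.3 is the total effect and a quarter to three quarters of it precedes t0, power falls from about 72% to between 48% and 9%. This rests on an assumed f, AR(1) correlation, linear dropout and two-sided 0.05. The conclusion about the estimand needs none of these; it requires only that some RC impact may precede t0, which the protocol itself allows.

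**What to change.** 1. In Analysis study 1A, delete the parenthetical label. State that the t0 group difference is read as a mix of selection and possible prior RC benefit.
2. Define the group-by-time estimate, and the responder outcome in Analysis study 1B, as further change over 24 months among current attenders. State that a null on either does not show RC attendance to be ineffective, and align the answer to RQ 1 with this.
3. If start of attendance is not already recorded, ask RC participants for the month and year of first attendance at the earliest remaining wave. Pre-specify a time-by-prior-duration term within the RC arm; controls have no duration at t0, so a three-way term with group would be undefined. As a sensitivity analysis, compare recent starters with their matched controls, fixing the cut-off for recent before the outcome data are examined.

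Items 1 and 2 cost only wording. Item 3 costs at most one survey question and one model term. Its limits should be stated: recent starters will be a small subgroup with a wide interval, and start dates will be missing for those who dropped out earlier.

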#### Analysis study 1B: economic evaluation

The economic evaluation will constitute both a cost-effectiveness analysis (CEA) and a cost-utility analysis (CUA). In line with the Dutch guidelines, a societal perspective will be adopted indicating that all costs should be included, regardless of who carries these costs [69]. Hence, four types of costs will be included (all expressed in Euros), namely (1) intervention costs, (2) patient and family out of pocket costs, (3) mental health care services costs and (4) costs due to productivity loss. Intervention costs will be estimated with input from experts coordinating RCs. Patient and family out of pocket costs refer to costs from help and support provided by the informal network of someone [70]. To determine costs the most recent costing manual will be used (at the time of writing this is [70]), with applied indexation if needed. Finally, costs of productivity loss include costs of absenteeism and presenteeism (i.e., being present at work but less efficient) of paid employment and volunteer jobs and will be determined by means of the friction cost method [71]. Since our data collection covers a time period of two years, costs will be indexed to the starting year 2022.

For the CEA, the primary outcome will be a proportion of responders based on the NEL after 24 months, which refers to whether or not participants (both experimental and control group) show a significant difference in self-reported empowerment at t_4_ as compared to t_0_. This variable will be dichotomized using the reliable change index by Jacobson and Truax [72]. For the CUA, the primary outcome will be the total incremental QALYs during the study’s timeframe of 24 months. Cumulative costs will be calculated based on this same time period.

To determine the cost-effectiveness of RC attendance, incremental cost-effectiveness ratios (ICERs) will be calculated for both the CEA and CUA, following Drummond, Sculpher [73]: ICER = (Costs^RC^ – Costs^control^)/(Effects^RC^ – Effects^control^). These ICERS are representative of average incremental costs associated with one additional unit of the measure of effect. Thus, the ICERs of the CEA represent the incremental costs per significant change in self-reported empowerment, and the ICERs of the CUA refer to incremental costs per QALY gained. Analysis will be done according to the intention-to-treat principle. We will use single imputations nested in non-parametric bootstrapping (N > 2500 bootstrapped samples) combined with seemingly unrelated regression equations [65]. Next, incremental costs, incremental effects and ICERS will be calculated. Sensitivity analyses will be conducted to assess the robustness of the findings, for example by running an analysis from the health care perspective (excl. patient and family costs, informal costs and productivity losses) [73].

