#### Variables of interest study 1B: economic evaluation

***Resource Use.*** To assess (informal) care use of participants, the Trimbos and iMTA questionnaire on Costs associated with Psychiatric illness (TiC-P; [58]) will be used, with a recall period of three months. This includes questions on medication and contact-hours with care providers but also questions about informal care received from one’s own social network (e.g., family, acquaintances, neighbours). To assess community outcomes such as employment, again the TiC-P [58] will be used. This includes questions on whether participants have employment or are active as volunteer, absenteeism and presenteeism of their (un)paid jobs. The recall period for absenteeism and presenteeism is four weeks. Housing status (e.g., living independently, living in a hospital/sheltered or supported housing residence, having no permanent residence) will also be determined by one item that we formulated (not in the TiC-P).

***Quality-Adjusted Life Years.*** In line with the Dutch guidelines for economic evaluations, quality-adjusted life years (i.e., QALYs) will be computed using utilities derived from the EuroQol-5-dimensions-5-level-questionaire (EQ-5D-5 L; [59]). The EQ-5D-5 L consists of six items, of which five inquire about specific restrictions in daily life (i.e., health states), with regards to mobility, self-care, usual activities, pain/discomfort and anxiety/depression. Possible answers on these items range from 1 to 5, where ‘1’ = Indicating no problem and ‘5’ = Indicating unable to/extreme problems. One final item regards the general health state (the EQ VAS: “We would like to know how good or bad your health is TODAY. Mark an X on the scale to indicate how your health is TODAY”). This general health state is represented by a number between 0 and 100, where ‘0’ = The worst health you can imagine, and ‘100’ = The best health you can imagine. The health states from the EQ-5D-5 L will be computed into utilities using the Dutch tariffs of EuroQol [60]. By means of the area under the curve method, time periods between assessment waves will be weighted by these utilities, which results in QALYs adjusted over the timeframe of 24 months. An overview of all measures can be found in Table 1.

**Table 1 Tab1:** Overview of all variables of interest and its matching instruments as used in Study 1

Measurement level	Variable of interest	Instrument	Reference
Primary	Empowerment	NEL	Boevink, Kroon (49)

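### The four listed cost types are narrower than the societal perspective they are meant to implement, and narrower than the resource use the study collects

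*Protocol article*

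**What the plan says.** In the protocol article, under Analysis study 1B: economic evaluation, the perspective is set first: "a societal perspective will be adopted indicating that all costs should be included, regardless of who carries these costs". The next sentence draws the consequence: "four types of costs will be included (all expressed in Euros), namely (1) intervention costs, (2) patient and family out of pocket costs", followed by "3) mental health care services costs and (4) costs due to productivity loss". The list is introduced as complete, with nothing to mark it as a set of examples. The second type is then defined: "Patient and family out of pocket costs refer to costs from help and support provided by the informal network of someone".

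Under Variables of interest study 1B: economic evaluation, the Resource Use paragraph describes the TiC-P: "This includes questions on medication and contact-hours with care providers". No restriction to mental health providers is stated. The same paragraph adds housing status, with categories that include "living in a hospital/sheltered or supported housing residence", measured by a single item written by the study team.

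The sensitivity analysis from the health care perspective, also under Analysis study 1B, is defined by what it removes: patient and family costs, informal costs and productivity losses.

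**The concern.** The article names a perspective in which every cost counts, whoever bears it, and then fixes a list in which the only formal care is mental health care. A health economist who follows the list as written would report a partial cost measure under a societal label.

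This bears on research question 3, because these costs form the numerator of both ratios. In the cost-utility analysis it also creates an asymmetry. QALYs come from the EQ-5D-5L, which asks about mobility, self-care and pain, so physical health enters the effects while somatic care would be missing from the costs. The Background places Recovery Colleges alongside social services as well as health care, so moves of cost between these budgets are part of what the project wants to understand. A change between supported and independent living would not register in the cost total if housing has no cost type.

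**Working it through.** The documents state no cost total, unit price or cost-effectiveness ratio, so there is no figure to reproduce. The check sets what is collected against what is listed, and then follows the consequence through the article's own formula.

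**Step 1. Match each resource item to a listed cost type, by label.**

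| Item under Resource Use (study 1B) | Cost type that names it |
|---|---|
| Contacts with mental health providers | Type 3, mental health care services |
| Contacts with other care providers | None |
| Medication | None by name; medication for mental health could be read into type 3 |
| Informal care | Type 2, by its definition |
| Absenteeism and presenteeism, paid and volunteer work | Type 4, productivity loss |
| Sheltered or supported housing | None |

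Type 1 covers the intervention only. Type 2 cannot serve as a remainder category, because the article defines it as help from the informal network.

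**Step 2. Derive the health care perspective.** Start from the four types. Remove patient and family costs (type 2) and productivity losses (type 4). Two types remain: intervention and mental health care services. Somatic care has no place here either, although it belongs in a health care perspective by its ordinary meaning. The exclusion list also names informal costs separately from patient and family costs, although type 2 is defined as informal help. The cost categories therefore do not line up between the two paragraphs.

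**Step 3. Effect on the ratio.** The article defines ICER = (C_RC − C_control) / (E_RC − E_control). Let O be the mean cost per person in the categories left out. Then

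ICER with all costs − ICER on the listed costs = (O_RC − O_control) / (E_RC − E_control).

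The documents give neither the numerator nor the denominator of this shift, so its size and sign cannot be stated. If O_RC = O_control, it is zero.

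**Step 4. Can the planned adjustment repair it?** Housing is not among the matching variables (Procedures, Matching). The Analyses section provides that baseline differences left after matching are checked and adjusted for where necessary. Such adjustment makes the groups more comparable on the costs that are counted. It does not add a cost that was never counted.

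**The case against.** The strongest reply is that the omission is inferred from labels. Nowhere does the article say that somatic care, medication or housing is excluded. The TiC-P contacts are not restricted, the costing manual is to be used to determine costs, and calling the reduced set a health care perspective suggests that type 3 may be meant broadly. The Satisfaction with Care and Support paragraph adapts an inventory to mental health care and still names the general practitioner as a provider, so the authors may count such contacts within type 3. Housing also has another stated use, as a descriptive variable. Finally, an article may leave the assignment of items to unit prices to a fuller plan that is not shown.

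Much of this stands. A reader might infer that these costs are definitely left out and that the ratio is therefore biased. The documents do not support that: intent is not stated, and bias needs a between-group difference in the omitted costs. Nor do they support any euro amount, or any claim about how large housing or general care costs are relative to mental health care.

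What does not stand is that this is only missing detail. Unit prices may be left to another document, but here the article itself fixes the cost types, presents them as following from the perspective, and they do not cover it.

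**Conclusion.** The point holds as a mismatch between a stated perspective, a stated closed list and the data collected. Taken literally, the list gives a societal ratio and a health care perspective that are both narrower than their names. This rests on reading type 3 as its label says; if the authors mean all health care, the defect on that part is one of wording, and housing still has no cost type. No magnitude can be given: the effect is unknown in size and direction and may be zero. It should be corrected before costs are analysed, because the underlying data are already being collected.

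**What to change.** In Analysis study 1B:

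1. Change the third cost type to health care costs, mental and other, valued from all TiC-P contacts and medication.
2. Add residential costs for sheltered or supported housing, taken from the housing item. One status item does not measure days, so state the approximation: status at a wave is applied to an interval. With five assessments there are four six-month intervals, so the plan must say which wave governs each one. Do not count inpatient care from the TiC-P a second time. If days cannot be approximated credibly, move this component to a sensitivity analysis.
3. Define the health care perspective from the full health care category, and use the same category names in both paragraphs.
4. If any of these costs cannot be valued, narrow the name of the perspective and report which costs are excluded.

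The cost is more costing work, approximate housing days and a somewhat wider interval for total costs. No new data collection is needed for these categories.
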